***Sample Size Determination***

No sample size calculations have been performed because this pilot study has not been powered to achieve outcomes that are statistically significant. We have chosen a sample size of forty-two participants because it is a reasonable number of persons to pilot the intervention/new protocol, SUCCESS, to show feasibility.

***Endpoint Definitions***

Time to linkage to care will be defined as the time from release to visit with an HIV provider, as evidenced by laboratory results indicating measurement of an HIV viral load and/or CD4 count.

***Statistical Analyses***

Linkage will be assessed for each individual at 3 months post-release from their index incarceration—how much time passed after release before the participant kept an appointment in an HIV clinic. Subjects will be followed from the day they are released, and the number of releasees who have linked to care every 30 days will be assessed at 3 months. The day of the first laboratory draw post-release will be considered the time point at which linkage occurs. A Kaplan-Meier curve with associated 95% confidence interval will be used to estimate the linkage rates for the participants. The proportion of persons retained in care will be presented with its associated 95% confidence interval.

1. **Training**

[name] has conducted 2 days of face-to-face training with the project coordinator, [name], and [name]. The newly hired study CM, trained at the minimum at a Bachelors level in an appropriate field, and with case management experience, will undergo training by [name] (via Skype) and [name] to ensure that they understand the basic principles of the *ARTAS* approach and can implement the intervention with fidelity to the conceptual model and the protocols. All CMs will also receive training in administration of the informed consent process and a brief baseline survey. Having the intervention staff, rather than a separate, independent assessment team, administer the baseline survey is a concession that reflects the complexity of having multiple staff members connect with clients within the jail. At the end of the training period, all intervention staff will demonstrate comprehension of the three principles of SBCM (and how they relate to the factors inherent in the conceptual model. CMs will have a refresher training session once during the intervention period.

1. **Data Safety and Monitoring Plan**

A formal DSMP is not applicable for this demonstration project.

1. **Confidentiality**

All participant information will be kept private. Upon enrollment in the study, the participant will be assigned a study identification number in which all information will be tracked. Participant information will be stored in locked cabinets and on password protected computers. Access to the project data management system will only be given study staff/researchers with individual, private logins and passwords.

1. **Informed Consent**

Upon successful completion of an eligibility assessment, study participants will be asked by study staff to participate in the study. Study participants will be given a written Informed Consent Form which will be read to them by the study staff person at which time if the participants agree, will sign. Study participants may opt out of the study at any time. Site staff has been instructed not to recruit inebriated inmates. Once enrolled into the study, participants will be assigned to the case manager who will provide all case management services.

1. **Plans to Inform Participants of New Findings**

The study researchers will disseminate findings from this study in both scientific and lay formats. The study staff persons or community base partners will attempt to contact clients about results that might affect their health.

| Table. Project Timeline: ***Preliminary Planning for SUCCESS*** | Q1 | Q2 | Q3 |
| --- | --- | --- | --- |
| Finalize IRB Approval & Certificate of Confidentiality. Hire/train staff. | √ |  |  |
| Recruit 14 subjects/month, start SBCM in jail x 3 months (N=42). |  | √ |  |
| Deliver SBCM for 60-day post jail release. |  | √ | √ |
| Conduct 3 month chart review of participants. |  |  | √ |

REFERENCES

**3.** U.S. Preventative Services Task Force. Screening for gonorrhea. <http://www.ahrq.gov/clinic/uspstf/uspsgono.htm>. Accessed 07/22/2008.

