This proposed project, ***Preliminary Plans for SUCCESS*** (**Sustained, Unbroken Connections to Care, Entry Services, and Suppression)**, will test the logistics and acceptance of the intervention. For the present study, we aim to explore if **SUCCESS** recipients will link to care at rates that match nationwide norms for the non-incarcerated. Findings from this feasibility study of **SUCCESS**, if successful, will address a gap in the literature by informing the planning of a novel randomized clinical trial to examine long-term effectiveness and cost of intensive case management, as compared with usual care for the hard-to-treat population of jail detainees.

**Aim 1. Connection to care:** Recruit HIV+ jail detainees at a pace of 14 per month for 3 months, deliver Strengths-Based Case Management in jail and during the first 60 days in the community (reinforced with cell phone contact upon release), and demonstrate that enrolled releasees will link to HIV care by 3 months post release. A successful linkage to HIV medical care will be defined as a confirmed visit to a clinic post release, validated by a recorded HIV viral load and CD4 count in the clinic’s medical records.

*Hypothesis: 75% of* ***SUCCESS*** *participants will link to HIV medical care by 3 months post-release.*

**Aim 2. Sustain a testing and linkage program:** Having linkage services available is crucial to the success of the testing demonstration project. Success with the testing program this year will ensure that the company will underwrite continued testing in the future, which we will benefit our future studies of the linkage intervention. The goal for next year is to conduct a full scale feasibility study that is dependent on continued industry support of testing. The ultimate goal is to prepare a protocol for testing SUCCESS in a randomized controlled trial and to conduct that study.

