***Outcomes measurement:*** The primary outcome will be whether a participant linked to community HIV care and, if it occurs, how long before a linkage occurred, with the clock starting at the initial release from jail. Linkage to care will be defined as a visit to an HIV provider that entails the acquisition of an HIV viral load and CD4 cell count. This outcome will be assessed at 3 months and will be measured in days between initial jail discharge and laboratory draw. This measurement will be adjusted for the number of days at liberty, since participants may return to jail one or more times in those 3 months post initial release. The interval of 3 months post initial release, rather than a shorter period, is warranted because participants who had a medical visit within a month prior to incarceration and, upon release, returned to the clinic within 3 months of their last visit, would still be considered linked to care by national performance guidelines[^69^](#_ENREF_69) **Chart review.** The study team will review the jail medical records and the community HIV medical clinic records at 3 months in order to gather data on whether a face to face visit occurred with a provider and whether laboratory tests (CD4 and HIV RNA) were ordered.

1. **Risks to Participation**

Potential discomfort or risk to a subject includes 1) psychological distress if a participant feels coerced to participate, and 2) breach of confidentiality of health information. This research does not adversely affect a participant’s rights and welfare, provided that the confidentiality of identifying information is maintained. The two potential risks listed above will be addressed in the following manner:

1. Subjects may experience psychological stress if they feel coerced to participate. However, the likelihood of this risk is small. When the study team solicits informed consent, potential participants will be told that their enrollment is voluntary. Furthermore, enrolling in the study will not affect the conditions of any parole or probation. Participant incentives in this study are nominal and will be given to participants only after reentry to the community. Participants may separate from the study at any point without any penalty.

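### Linkage, the primary outcome, is defined inconsistently: both tests or either test, visit date or draw date, and a dating rule that names neither test nor site

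*Protocol*

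**What the plan says.** Under Measures the protocol sets the outcome: "The primary outcome will be whether a participant linked to community HIV care", together with the time this takes, counted from initial release. Linkage is then described in four sections.

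- **Specific aims, Aim 1:** a confirmed clinic visit after release, "validated by a recorded HIV viral load and CD4 count" in that clinic's records.
- **Measures, outcomes text:** "a visit to an HIV provider that entails the acquisition of an HIV viral load and CD4 cell count", timed in days from initial discharge to the laboratory draw. The same paragraph expects some participants to go back to jail during the 3 months. Its chart-review item covers jail and clinic charts and records whether a provider was seen face to face and "whether laboratory tests (CD4 and HIV RNA) were ordered".
- **Endpoint Definitions:** time from release to the visit with an HIV provider, "as evidenced by laboratory results indicating measurement of an HIV viral load and/or CD4 count".
- **Statistical Analyses:** time until an HIV-clinic appointment was attended, with no laboratory condition, followed by "The day of the first laboratory draw post-release will be considered the time point at which linkage occurs". These times feed a Kaplan-Meier curve and counts of linked participants at 30-day steps.

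Aim 1 states the hypothesis that 75% of participants will link by 3 months.

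**The concern.** The sections do not agree on who is linked or on which day. A participant whose visit produced only a viral load is unlinked under Aim 1 and Measures, and linked under Endpoint Definitions. A participant seen by a provider shortly before the 3-month cut-off, whose blood is drawn shortly after it, is linked in time by the visit date and not by the draw date. The rule that sets the date restricts neither the test nor the place. The planned abstraction item (ordered) cannot supply the recorded results that Aim 1 requires or the draw date that the analysis needs.

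On who counts, the looser readings can only add linked participants, so this is a one-directional shift that a confidence interval does not show. The study is also meant to supply preliminary data for the power analysis of a later randomized trial, so the ambiguity would carry into that trial's assumed rate. Choosing among the readings after the charts have been seen could decide on which side of 75% the estimate falls.

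**Working it through.** **The plan's own figure.** 14 recruits per month × 3 months = 42, which agrees with the stated sample size. The protocol gives no alpha, power or margin, so there is nothing further to reproduce.

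**The text set side by side.**

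1. *Which tests:* both (Aim 1; Measures), either (Endpoint Definitions), none mentioned (the attended-appointment wording in Statistical Analyses). Both versus either is a direct contradiction.
2. *Which date:* visit (Endpoint Definitions), draw (Measures), attended appointment and then first draw (Statistical Analyses).
3. *Which site:* community or clinic in Aim 1 and Measures; not stated in the dating sentence. No sentence excludes a draw in custody.
4. *What is abstracted:* tests ordered, against tests recorded in Aim 1.

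**What one participant is worth.** 1/42 = 2.4 percentage points. The hypothesis corresponds to 0.75 × 42 = 31.5 participants.

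- 31/42 = 73.8%, exact 95% interval 58.0% to 86.1%
- 32/42 = 76.2%, exact 95% interval 60.5% to 87.9%

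One reclassification therefore moves the point estimate across 75%, within an interval about 28 points wide.

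**Draws in custody.** The only input in the protocol is a 16.1% return to jail within a year (Local jail data), which covers all releasees and not only those with HIV. Assuming a constant hazard, return within 3 months is 1 − (1 − 0.161)^(1/4) = 4.3%. The added share is P(return) × P(not otherwise linked) × P(HIV blood drawn in jail), with return and linkage taken as independent and the last probability assumed to lie between 25% and 100%.

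- 75% truly linked: 0.043 × 0.25 × (0.25 to 1) = 0.3 to 1.1 points, or 0.1 to 0.5 people.
- 75% linked, and all 16.1% return within 3 months: 1.0 to 4.0 points, or 0.4 to 1.7 people.
- 59% linked (the rate the protocol reports for EnhanceLink), all 16.1% return within 3 months, and every returner has blood drawn: 0.161 × 0.41 × 1 = 6.6 points, or 2.8 people.

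Independence may be optimistic. If no returner linked otherwise and all had blood drawn, the constant-hazard figure is 0.043 × 42 = 1.8 people.

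**Both tests versus either test.** The protocol does not say how often only one test is done. If linkage under the either-test reading is 75% and a share s of those visits has a single test, requiring both lowers the estimate by 0.75 × s:

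- s = 2%: 1.5 points (0.6 people)
- s = 5%: 3.8 points (1.6 people)
- s = 10%: 7.5 points (3.2 people)

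These shares are assumptions.

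**The case against.** The strongest reply is that the protocol is clearer than isolated sentences suggest. Aim 1 and the outcomes text agree in substance, the chart-review line describes data collection, and the first-draw sentence dates an outcome already defined elsewhere. A reader might infer four incompatible definitions. The documents do not support that count: the clear conflict over who is linked is both tests versus either, alongside an appointment wording with no laboratory condition and an unsettled event date.

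A reader might also infer that blood drawn in jail after re-arrest would be counted. That follows only if the dating sentence is read alone. The outcome is community care, Aim 1 looks to the clinic's records, and the same paragraph of Statistical Analyses speaks of an HIV-clinic appointment. Reviewing jail charts does not show that jail draws count. What stands is that they could be counted, because nothing expressly excludes them.

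A third tempting reading is that case-management sessions held at the clinic could pass as linkage. The description of the sessions separates them from medical visits, and Measures and Endpoint Definitions both refer to a provider.

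Finally, this is a single-arm feasibility study with no power calculation. It plans estimation with a confidence interval, attaches no test or go/no-go rule to 75%, and also reports retention in care. To say that the definition turns a pass into a fail, or that linkage is the only effectiveness-type outcome, goes beyond the text. None of this reconciles the sections, and the protocol fixes the endpoint itself, so the contradiction is not a detail left to a statistical analysis plan.

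**Conclusion.** The point holds in this form. As written, the primary outcome cannot be computed uniquely, because the sections differ on the tests required and on the event date, the dating rule is silent on test and site, and the abstraction item is too weak for the definition it serves.

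The overall size cannot be derived from the protocol. What is certain is 2.4 points per reclassified participant, with 31/42 and 32/42 on either side of the 75% hypothesis; that contrast shows sensitivity and is not a decision the protocol makes. Draws in custody probably account for 0 to 2 of 42 participants, given the all-releasee return figure, a constant hazard and assumed jail-draw frequencies. The both-versus-either question could matter more, but its size rests wholly on assumed shares of single-test visits.

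**What to change.** Before chart abstraction begins, use one definition in Aim 1, Measures, Endpoint Definitions and Statistical Analyses.

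- **Definition:** the natural choice is the one already in Aim 1 and Measures, namely a visit to an HIV provider in the community after initial release, with both viral load and CD4 recorded in the clinic's records. In Endpoint Definitions, replace and/or by and. Report the either-test version as a labelled sensitivity analysis.
- **Event date:** use one date throughout, for example the draw belonging to that qualifying visit, in place of the first draw after release.
- **Custody:** state that draws in custody do not count as linkage to community care.
- **Abstraction:** change the item from ordered to collected and resulted, with dates.

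The cost is protocol wording and one field on the abstraction form. The linkage figure may come out slightly less favourable.
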